## Abstract

**Background:**

Although many electrocardiography wearable devices have been released recently for the detection of atrial fibrillation (AF), there are few studies reporting prospective data for wearable devices compared to the strategy of the existing guidelines in the detection of atrial fibrillation (AF) after cryptogenic stroke. A tiny single-patch monitor is more convenient than a conventional Holter monitor recording device and, therefore, longer duration of monitoring may be acceptable.

**Methods and Design:**

The CANDLE-AF study is a multicenter, prospective, randomized controlled trial. Patients with transient ischemic attack or ischemic stroke without any history of AF will be enrolled. The superiority of the 72-h single-patch monitor to standard strategy and non-inferiority of the 72-h single-patch monitor to an event-recorder-type device will be investigated. Single-patch monitor arm will repeat monitoring at 1, 3, 6, and 12 months, event-recorder-type arm will repeat monitoring twice daily for 12 months. The enrollment goal is a total of 600 patients, and the primary outcome is the detection of AF which continues at least 30 s during study period. The secondary outcome is the rate of changes from antiplatelet to anticoagulant and major adverse cardiac and cerebrovascular events within 1 year.

**Conclusions:**

The results of CANDLE-AF will clarify the role of a single-lead patch ECG for the early detection of AF in patients with acute ischemic stroke. In addition, the secondary outcome will be analyzed to determine whether more sensitive AF detection can affect the prognosis and if further device development is meaningful. (cris.nih.go.kr KCT0005592).

## Introduction

For stroke patients, the American/European Stroke Society recommends 24–72 h rhythm monitoring for detecting atrial fibrillation (AF) as well as additional monitoring with long-term noninvasive monitors or implantable loop recorders (ILRs) if the cause of the stroke is unclear (1–4). The recently issued European Society of Cardiology 2020 AF guideline (3) recommends intensive electrocardiogram (ECG) monitoring in high-risk patients older than 75 years (Class of recommendation: IIa). ILRs can monitor the ECG rhythm 24 h a day for more than 3 years and can detect AF considerably more often than stepwise additional monitoring including 24-h Holter, which is the guideline-based standard method (12.2% vs. 2.0% and 30% vs. 3% in 12 and 36 months, respectively, after cryptogenic stroke; *n* = 221 vs. 220; *p* < 0.001) (5–7). However, because ILR insertion is an invasive procedure, not all patients receive ILR monitoring. The Early Treatment of Atrial Fibrillation for Stroke Prevention Trial (EAST-AFNET 4) (8) showed that early rhythm control of AF improved major clinical outcomes. Therefore, the development of a convenient, effective, noninvasive ECG monitor is valuable for diagnosing post-stroke AF.

Although the accuracy, sensitivity, and specificity of single-lead ECG recording have improved (9), few prospective studies have compared the AF-detection rates between different types of single-lead ECG recorders in patients with cryptogenic stroke. Studies such as the Apple Heart Study (10), REHEARSE-AF (REmote HEArt Rhythm Sampling using the AliveCor heart monitor to scrEen for Atrial Fibrillation) (11), and the SCREEN-AF (SCREENing for Atrial Fibrillation) (12) proved the usefulness of single-lead ECG, their results were based on data from the general population and not data that was specifically obtained from patients with an ischemic stroke or transient ischemic attack (TIA). In 2020, a study of nurse-led monitoring during stroke (SPOT-AF) demonstrated the feasibility and efficacy of a single-lead ECG recorder for post-stroke AF detection (13). A prospective study for comparing the event recorder (2 times daily) with a 7-day Holter monitor is ongoing (14).

According to the 2020 guideline of the European Society of Cardiology (3), single-lead ECG recording using a wearable device can be used for confirming a diagnosis of AF (Class of recommendation: Ia). A recent systematic review and meta-analysis suggested a noninvasive rhythm-monitoring strategy prior to invasive monitoring (15). Against this background, we designed a trial that compares a single-lead patch to an event-type recorder and standard care, respectively. We aimed to determine whether a single-lead patch-type ECG recorder is superior to the standard methods and to ascertain the non-inferiority of single-lead ECG patch recorder to an event recorder for early detection of AF in high-risk patients who have experienced an acute stroke and, thereby, facilitate an early switch from antiplatelet to anticoagulant medication based on the findings and other clinical conditions. Consequently, in this study, we intend to 1) reveal the clinical utility of a single-lead patch ECG for AF detection in patients who have experienced acute stroke; 2) identify whether single-patch ECG monitoring has possibility to be another widely used monitoring method for the detection of AF after cryptogenic stroke; and 3) explore, as a pilot study, the effect of the difference in the detection rate of AF on the recurrence of TIA or ischemic stroke and major adverse cardiovascular and cerebrovascular events (composite of nonfatal stroke, nonfatal myocardial infarction, and cardiovascular death) in patients with AF after stroke.

## Materials and Methods

### Trial Design

The Clinical implications of Atrial fibrillatioN Detection using a wearabLE device in patients with cryptogenic stroke (CANDLE-AF) study is a multicenter, prospective, open-label, randomized, controlled trial for detecting AF in post-stroke patients who have not been previously diagnosed with AF (reg. no. cris.nih.go.kr KCT0005592). Following the detection of AF in patients with cryptogenic stroke, we will conduct a superiority trial of single-lead patch ECG monitoring against standard monitoring and a non-inferiority trial of single-lead patch ECG monitoring against event-recorder type monitoring.

### Primary Objectives

For 12 months, this trial will investigate the superiority and non-inferiority of a 3-day continuous single-lead ECG patch in the detection of AF after stroke or TIA in comparison with the conventional strategy (guideline-based group) and event-recorder type monitoring, respectively.

### Secondary Objectives

In each group, we will evaluate the rate of change from antiplatelet therapy to anticoagulants following AF detection and the rate of major adverse cardiovascular or cerebrovascular events, which include all-cause mortality, stroke or TIA, and all-cause hospitalization and major adverse cardiovascular events (composite of nonfatal stroke, nonfatal myocardial infarction, and cardiovascular death). As the treatment policy will be changed in accordance with the detection of AF, we will assess the change in the incidence of recurrent stroke within 6 months/12 months of the initial stroke in each group.

### Study Population and Randomization

Seven tertiary hospitals with stroke units in South Korea will participate in this trial and these centers represent a full coverage of all levels of care, including state-of-art tests, monitoring, imaging equipment, the latest treatment policies of specialists, and intensive care units. All patients who first visit the department of neurology with a stroke or TIA without history of AF at the time of admission and if no AF was detected during monitoring of the hospital stay will be enrolled in this study after obtaining voluntary informed consent. In this study, by referring to the inclusion criteria used in CRYSTAL-AF (16), the minimum symptoms required for inclusion by TIA were established: speech or language deficit, weakness of an arm or leg, or hemianopsia. As an inclusion criterion, history of AF was established as a person who did not have AF at the time of admission and who had no prior AF diagnosis. A surface ECG at hospitalization will be used as the screening test to check for pre-existing AF. During the hospital stay, continuous ECG monitoring will be performed through telemonitoring. Before being discharged, all enrolled participants will be randomized to the: 1) the standard treatment group, 2) the single-lead ECG patch group, and 3) the event-recorder group. The exclusion criteria are described in Figure 1. We performed block randomization using random number generator function of Excel (Microsoft, USA). The randomization ratio is 1:1:1.

**Figure 1 F1:**
[figure not shown]
Flow chart of the study design. AF, atrial fibrillation; TIA, transient ischemic attack; MACCE, major adverse cardiovascular and cerebrovascular events (composite of nonfatal stroke, nonfatal myocardial infarction, and cardiovascular death).

### Two Types of Single-Lead ECG Monitors

A recently developed wearable device for the detection of arrhythmia, the adhesive single-lead ECG patch (mobiCARE-MC100 TM, Seers Technology, Seongnam-si, Gyeonggi-do, Republic of Korea), which comprises a light chest patch weighing 9.2 g without any other additional parts, allows long-term continuous ECG monitoring and is relatively more comfortable than standard Holter monitoring (Figure 2A). In a study comparing this single-lead patch monitor and Holter by wearing them simultaneously for 24 h, most patients did not feel discomfort with single-lead patch monitor (17). Based on these results, it is thought that the single-lead patch was more comfortable than the Holter. Monitoring is possible for up to 72 h when the patch is used once, and it is possible to continue the monitoring even when the battery has been replaced. Patients can check their ECG through a mobile phone application and the ECG will be automatically transmitted to a core laboratory. This single-lead ECG patch uses an artificial intelligence-based algorithm to systematically classify and analyze data to improve diagnostic accuracy. Furthermore, this device has an advantage in terms of signal accuracy because it has excellent ability to remove motion artifacts that may be mistaken for a heartbeat. According to a comparative study where a Holter monitor and the abovementioned single-lead ECG patch were simultaneously attached to non-arrhythmic patients, the intraclass correlation coefficients for total QRS complexes, ventricular ectopic beats, and supraventricular ectopic beats of the two devices were 0.991, 0.999, and 0.966, indicating that the performance of the two devices did not differ significantly (17).

**Figure 2 F2:**
[figure not shown]
Two types of wearable devices in this study. **(A)** Single-lead ECG monitor (mobiCARE-MC100 TM) which is attached by replaceable adhesive ECG electrodes, **(A)** Single-lead event recorder type monitor (KardiaMobile systemTM) being used with finger of right and left hand touching the respective electrode and showing sample ECG rhythm in mobile phone display. Copyright with permission from Seers Technology **(A)** and Alivecor **(B)**.

An event recorder-type ECG device based on a smartphone (Kardia Mobile TM, Alivecor Inc., San Francisco, CA, USA) has been developed (Figure 2B) and can enable the patient to measure and transmit the heart rhythm for a specific number of times a day and has superior AF-detection ability when compared to routine care in non-AF patients (11). In our study, in addition to the superiority of the single-lead patch to standard monitoring, we intend to demonstrate the non-inferiority of the single-lead ECG patch type monitoring to the event-recorder type of monitoring.

The server to which the ECG is transmitted is managed by the manufacturer of each device, and access to the data is restricted to those authorized to handle the data related to patient care and this study by IRB approval. The device manufacturers had no role in the trial design, data accrual, or analysis.


**Table 1 T1:** Summarization of CANDLE-AF study protocol.

	**Enrollment**	**Hospital discharge**	**0 month**	**3 months**	**6 months**	**12 months**
Standard group			On-demand additional evaluation			
Smartphone-based monitoring group	Randomization	24-h Holter	Daily 2 times of monitoring by smartphone-based monitor			
Single-lead patch monitoring group			72-h single-lead patch #1	72-h single-lead patch #1	72-h single-lead patch #1	72-h single-lead patch #1

### Clinical Monitoring

For 12 months following hospitalization, the detection of AF recorded on the device, all-cause mortality, all-cause rehospitalization, and change to anticoagulation will be recorded at the outpatient visit or through a telephone call. The prevalence of stroke, cardiovascular disease, diabetes, hypertension, and heart failure will be ascertained using the International Classification of Diseases-10 code corresponding to the diagnosis in the medical record. Sex, age, and the results of general blood tests, biochemical tests, myocardial enzyme levels, echocardiography, and brain imaging tests performed during the hospitalization period will be recorded. It is intended to be used as a covariate when comparing differences in primary or secondary outcomes.

### Study Duration, Interim Analyses, and Early Termination

The difference in the detection rate of AF is the primary outcome. The device-based monitoring will be stopped when AF is detected. The secondary outcome is the rate of changes from antiplatelet to anticoagulant, major adverse cardiac and cerebrovascular events (composite of nonfatal stroke, nonfatal myocardial infarction, and cardiovascular death), and occurrence of major bleeding (fatal or overt bleeding with a drop in hemoglobin level of at least 2 g/dL or requiring transfusion of at least 2 units packed blood cells, or critical anatomical site hemorrhage (e.g., intracranial, retroperitoneal) within 1 year. For secondary outcome, the follow-up period is 12 months. Changes in antiplatelet and anticoagulant therapy will not affect clinical study discontinuation. Monitoring and follow-up will be terminated early if a skin disease occurs due to the patch, if the patient no longer wants to participate, or if it is impossible for the patient to participate due to causes, such as hospitalization due to a serious disease or death. When discontinuation or drop-out occurs, all data of the participants that were recorded up to that time point will be used, and patient data up to the point of interruption in the intention-to-treat strategy will be used for statistical analysis. If the participant does not want their data to be used, all of their data will be discarded and not used in the statistical analysis.

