### Current Status

The CANDLE-AF trial is planned to complete the 3-year enrollment period for the prespecified 600 participants from the 7 participating centers. The first participant was enrolled in November 2020, and~ 100 patients were enrolled by the end of November 2021. Enrollment may be completed in late 2023, and the primary results of the CANDLE-AF trial will be available by early or mid-2024.

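### The early-termination rule ends outcome follow-up as well as device use: after patch skin disease in the patch arm only, and in any arm when serious illness makes participation impossible

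*Protocol article*

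**What the plan says.** All of the following is in the protocol article.

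- **Study Duration, Interim Analyses, and Early Termination**, skin trigger: "Monitoring and follow-up will be terminated early if a skin disease occurs due to the patch".
- Same sentence, illness trigger: "if it is impossible for the patient to participate due to causes, such as hospitalization due to a serious disease or death". Withdrawal by the patient is the remaining reason.
- Same section, data then used: "patient data up to the point of interruption in the intention-to-treat strategy will be used for statistical analysis".
- Same section, intended period: "For secondary outcome, the follow-up period is 12 months". The secondary outcomes listed there are change to anticoagulation, major adverse events and major bleeding.
- Same section, a stop that concerns the device alone: "The device-based monitoring will be stopped when AF is detected".
- **Secondary Objectives** lists as outcomes "all-cause mortality, stroke or TIA, and all-cause hospitalization and major adverse cardiovascular events".
- **Clinical Monitoring** records device-detected AF, mortality, rehospitalisation and anticoagulation change for 12 months, at a visit or by telephone.
- **ECG Monitoring** and **Table 1** schedule the patch in one arm only.
- **Current Status**: "Enrollment may be completed in late 2023, and the primary results of the CANDLE-AF trial will be available by early or mid-2024".

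**The concern.** Stopping a device and stopping observation of the patient are different events. This rule joins them.

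The skin trigger can fire only in the patch arm, and it carries no condition on severity or on ability to take part. The illness trigger can fire in every arm, but those it removes are at higher risk of death, recurrent stroke, bleeding and a change of antithrombotic therapy. Censoring them at that point is unlikely to be independent of outcome, which matters for any time-to-event comparison.

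At stake are the later clinical events, anticoagulant changes and AF found on ECGs other than the study device. Under-counting in the patch arm alone would make that arm look slightly safer. No later analysis can recover events that were never collected.

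**Working it through.** **1. The passages side by side.** The section uses a narrow term for the stop at AF detection (device-based monitoring) and a wider one for early termination (monitoring and follow-up). The plain reading is that the second ends outcome collection too, and the statement that data up to the interruption are used confirms it. Nothing in the article resumes collection afterwards. This does not fit the 12-month period in the same section, nor the visit or telephone route in Clinical Monitoring, which a skin reaction does not prevent.

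**2. The plan's own sample size, for the inputs used below.** Sample-Size Estimates assumes detection of 14.5% (patch), 8.5% (smartphone recorder) and 2.5% (standard), a margin of 2.3%, alpha 5% and power 80%. With unpooled variance and one-sided alpha 0.05:

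- Non-inferiority: n = (0.145×0.855 + 0.085×0.915) × ((1.645 + 0.842)/(0.060 + 0.023))² = 181.1, so 182. Adding 10% gives 201; dividing by 0.9 gives 203. Stated: 200.
- Superiority: n = (0.145×0.855 + 0.025×0.975) × ((1.645 + 0.842)/(0.120 − 0.023))² = 97.5, so 98. Adding 10% gives 108; dividing by 0.9 gives 109. Stated: 108.

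Both reproduce, and neither is disputed here.

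**3. Clinical outcomes under the skin trigger.** The article gives no skin-reaction rate. Let s be the share of the patch arm stopped and f the fraction of their events that fall after the stop. Assume equal true risk in both arms and the same risk in stopped patients. The observed risk ratio is then 1 − s×f, whatever the underlying risk.

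| s (assumed) | f = 0.5 | f = 1 |
|---|---|---|
| 2% | 0.99 | 0.98 |
| 5% | 0.975 | 0.95 |
| 10% | 0.95 | 0.90 |

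In event counts: the Discussion cites 12-month recurrent stroke of 3.7% and 5.4% in an earlier trial. In 200 patients that is 7.4 to 10.8 strokes. At s = 5% the number hidden lies between 7.4 × 0.05 × 0.5 = 0.2 and 10.8 × 0.05 × 1 = 0.5.

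**4. Primary outcome under the skin trigger.** Suppose stopped patients lose a fraction f of their detections and count as not detected. Patch detection becomes 0.145 × (1 − s×f), and power = Φ((difference + 0.023)/SE − 1.645). With 200 analysed per arm and no stopping, SE = √(0.20175/200) = 0.03176 and power = Φ(0.083/0.03176 − 1.645) = 83.4%. With f from 0.5 to 1, non-inferiority power is:

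- s = 2%: 82.4% to 81.3%
- s = 5%: 80.8% to 78.0%
- s = 10%: 78.0% to 71.6%

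These figures combine lost patch sessions with lost follow-up. Continued follow-up would restore only AF found on other ECGs, so they overstate what the follow-up rule itself costs.

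**5. Illness trigger.** The article gives no rate and does not say how often an admission would make participation impossible. No size is calculated.

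**6. Dates.** Late 2023 plus 12 months is late 2024. The forecast readout is early or mid-2024.

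**The case against.** The strongest case on the other side is that the loss is small and much of it is not caused by this rule. Most of that stands.

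- **Hospitalisation.** A reader might infer that every serious admission ends follow-up. Assuming 10% to 30% of patients are admitted, evenly over the year, that would cost 10% × 0.5 = 5% to 30% × 0.5 = 15% of person-time. The text does not support this: the condition is that participation is impossible, and admission is an example. Sample-Size Estimates allows 10% drop-out in all. Data up to the interruption are kept, so the triggering admission can itself be counted.
- **Intention-to-treat.** A reader might infer that the rule breaks this principle. It does not exclude anyone for stopping early: patients stay in their randomised arm with data to the interruption. The fault is incomplete follow-up.
- **Primary outcome.** Sessions lost to skin disease belong to the monitoring strategy under comparison, and the fix does not bring them back. If such patients count as not detected, the skin trigger works against the patch in both comparisons, so it cannot by itself produce a false claim for the patch. The article does not say how they are classified, which an analysis plan commonly settles.
- **Clinical outcomes.** The Introduction describes the clinical-event aim as a pilot exploration.
- **Timetable.** A reader might infer that late enrollees will be analysed without 12 months of data. Current Status is a forecast, not a data-lock rule, and the date may simply slip.

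None of this answers the central point: a skin reaction is no reason to stop collecting outcomes, and the stated rule does so in one arm.

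**Conclusion.** The concern holds in limited form. The protocol article ends outcome follow-up, not only device use, at patch-related skin disease and when participation is impossible, for example because of serious illness. The first trigger is confined to the patch arm and the second is related to the outcomes. Both sit badly with the 12-month follow-up stated in the same section.

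The effect is probably small. At an assumed 5% of the patch arm stopped, a true clinical-event risk ratio of 1.0 would appear as about 0.95 to 0.975, which is at most about half a recurrent stroke hidden in 200 patients. This rests on an undocumented stopping rate and on stopped patients having average risk. The illness trigger cannot be sized from the document. The point is worth correcting because the loss is irreversible and cheap to prevent; it does not by itself threaten the primary conclusion.

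The mismatch between the forecast readout and 12 months of follow-up for the last participants is a minor side point.

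**What to change.** In Study Duration, Interim Analyses, and Early Termination, separate the end of device use from the end of outcome follow-up:

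- Leave the device-discontinuation rules as the plan has them.
- State that outcome follow-up continues to month 12 through the visit or telephone call in Clinical Monitoring, except after death or withdrawal of consent to follow-up.
- State that hospitalisation does not by itself end outcome collection.
- Name what is still collected after device use ends: AF on any ECG, anticoagulation change, stroke or TIA, infarction, major bleeding, hospitalisation and death. Clinical Monitoring at present names only some of these, and for AF only what the device records.

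In Current Status, reconcile the readout date with 12 months of follow-up for the last participants enrolled.

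The cost is a short amendment and some extra telephone follow-up. If enrolment does end in late 2023, 12-month data are complete only in late 2024, so the forecast readout would move later. Patch sessions lost to skin disease are not recovered.
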